**Figure 1 figure1:**
[figure not shown]
Anticipated *Strong & Deadly Futures* trial flow based on the CONSORT guidelines.

#### Sample Size Calculations

The sample size has been calculated to account for cluster randomization using the methods developed by Heo and Leon [31] to detect group-by-time interactions in longitudinal cluster RCTs. To adequately power the trial for comparisons among Aboriginal and Torres Strait Islander students, a minimum of 264 Aboriginal or Torres Strait Islander students from 22 schools is required (ie, 12 Aboriginal or Torres Strait Islander students per school). This would achieve 80% power to detect a standardized between-group mean difference of 0.3 (*P*=.05) in primary alcohol (frequency of drinking a standard drink in the previous 6 months), tobacco (frequency of smoking a cigarette in the previous 6 months), and psychological distress (Kessler-5 Psychological Distress Scale) outcomes at the end of the trial with 4 measurement occasions. No effect size information was available for school-based prevention for Aboriginal and Torres Strait Islander students; thus, the estimated effect size of 0.3 was based on effects found for continuous alcohol outcomes in previous school-based prevention trials in mainstream populations [10,32]. Accounting conservatively for a higher student attrition rate than that observed in these trials of 30%, we will recruit 24 schools with an average of 16 Aboriginal or Torres Strait Islander students per school, and a total of 40 students per school. This totals 384 Aboriginal or Torres Strait Islander students, and a total sample of 960 students.

#### Inclusion Criteria

Eligible schools will have at least 12 Aboriginal or Torres Strait Islander students per grade in 2021. Although outcomes will be measured for all students, the primary analyses will be conducted among the Aboriginal subsample in line with the focus of the study. The recruited schools are expected to vary from approximately 10% to 100% of students identifying as Aboriginal or Torres Strait Islander. All students in year 7 and 8 attending the participating schools in 2022 will be eligible to participate, provided they provide opt-in consent and their parents provide opt-in or opt-out consent (dependent upon ethical requirements; see *Informed Consent*).

#### Procedure

##### Recruitment

We will recruit 24 schools across NSW, WA, and QLD during 2021. Researchers will identify and approach eligible schools using data from the MySchool website [33] beginning with those who have previously expressed interest in participating. School principals and health education staff will be emailed an invitation letter detailing the study aims and procedure, followed up by phone calls or emails from the research team.

##### Informed Consent

Once recruited, principals will be asked to provide written consent for the school to participate in the trial. Schools will distribute information and consent forms to parents electronically or by hard copy and will be required to obtain opt-in (QLD public and WA Catholic schools) or opt-out parental consent (NSW and independent schools), depending on the relevant ethical requirements. Where opt-in parental consent is required, school staff members will be reimbursed to follow a standardized script for obtaining verbal consent over the phone in cases where it is not feasible to obtain written consent from parents. Students will be provided with electronic participant information statements and consent forms before survey commencement. Only students with parental consent and who have assented will complete the survey assessments; however, all students in *Strong & Deadly Futures* schools will participate in the program, as it will be delivered as part of their usual drug education curriculum. Year 7 and year 8 health teachers will also be asked to consent to completing web-based logbooks as a measure of implementation fidelity and to permit facilitators to record their observations from the *Strong & Deadly Futures* lessons.

#### Strong & Deadly Futures Group

*Strong & Deadly Futures* is a 6-lesson web-based social and emotional well-being and AOD prevention program that aligns with the Australian year 7 and 8 curriculum and the NSW Stage 4 Syllabus for Health and Physical Education. Each lesson consists of a 10-minute illustrated story, a selection of classroom activities, and teacher and student lesson summaries [16]. Lessons take approximately 45-60 minutes to complete and are optimally delivered once a week for 6 weeks. Program content is based on the established harm minimization [34] and social influence [35,36] approaches to AOD prevention and targets key risk and protective factors identified in our systematic review of effective substance use prevention among Indigenous youth [15]. The individual lesson content and targeted factors are detailed in Multimedia Appendix 1. In brief, the 6 lessons address the following key learning outcomes:

Coping with psychological distress, seeking help, and building self-efficacy;AOD education: short- and long-term consequences, harm minimization, helping and coping with other people’s AOD use;Corrective information about normative peer alcohol and tobacco use, finding accurate information about AODs;AOD refusal strategies, coping with peer pressure;Positive alternatives to AOD use, role models.

Students and teachers can access *Strong & Deadly Futures* program content by creating accounts on the program website. Student accounts provide access to the illustrated stories and student lesson summaries. Teacher accounts provide access to the stories, teacher summaries, and class activity options (eg, prespecified worksheets, discussion topics, and activities). Teachers are provided with approximately 6 activity options for each lesson, one of which focuses on cultivating awareness of and pride in Aboriginal and Torres Strait Islander culture. Six months after the 6 lessons, 2 booster sessions will be delivered to help students refresh the content. Booster sessions will be delivered 1 week apart and follow the same structure as the original program.

#### Health Education as Usual Group

Participants in the *health education as usual* group will receive their usual curriculum-based health education classes in 6 weekly 45- to 60-minute lessons over a period of approximately 6 weeks. The Australian and NSW year 7 and 8 Health and Physical Education curriculum mandates that AOD use and social and emotional well-being content be implemented. As such, all *health education as usual* schools will implement curriculum-based drug education during the trial, which will naturally vary in the method of delivery, and serve as an *active control*. Alcohol and drug education in control schools may include tailoring for Aboriginal and Torres Strait Islander students and is expected to vary by school. Details of the content taught will be recorded in logbooks. These schools will be supported to implement the *Strong & Deadly Futures* program with year 7 and 8 students after all trial assessments are complete (from 2024).

#### Assessments

Students will complete self-report surveys at pre- and postprogram implementation and at 12- and 24-month follow-up to assess program effects. Given the preventive focus of the trial, the primary end point is 24 months post baseline to coincide with the peak onset of AOD use during middle adolescence [37]. All primary and most secondary measures were administered to students in our *Strong & Deadly Futures* pilot trial. Surveys will be accessed via electronic links and captured using REDCap (Research Electronic Data Capture; Vanderbilt University) electronic data capture tools hosted at the University of Sydney [38]. REDCap is a secure research data collection platform that links participant data over time while maintaining rigorous security controls to protect students’ privacy. Students will complete surveys in class and be assured by the teacher and facilitator that the data they provide are strictly confidential. If students are absent, teachers or facilitators will arrange an alternate time to complete the survey at school. Follow-up surveys will be sent to students automatically by REDCap using the contact details supplied during the first survey. Where ethical approvals permit it, students will enter into a draw to receive an Aus $ 30 (US $ 21.67) Prezzee gift voucher (1 or 2 per school, dependent on school size) per assessment occasion to maximize participant retention. The timeline schedule for trial participants is shown in Table 1.

**Table 1 table1:** Schedule of program implementation and assessments.

	Preprogram survey	*Strong & Deadly Futures*	Postprogram survey	Booster sessions	12-month follow-up survey	24-month follow-up survey
Period	Term 3 or 4, 2022	Term 3 or 4, 2022	Term 3 or 4, 2022	Term 1 or 2, 2023	Term 3 or 4, 2023	Term 3 or 4, 2024
School grade (age group in years)	7 or 8 (11-13)	7 or 8 (11-13)	7 or 8 (11-13)	8 or 9 (12-14)	8 or 9 (12-14)	9 or 10 (13-15)
*Strong & Deadly Futures* group	✓	✓	✓	✓	✓	✓
*Health education as usual* group	✓		✓		✓	✓

#### Demographics

Demographic variables will be recorded at baseline, including gender (*male*, *female*, *nonbinary* or *gender*
*fluid*, *different identity*, *prefer not to say*), age (12-16 years), school year (7-8), and whether students identify as Aboriginal (*Aboriginal*, *Torres Strait Islander*, *Aboriginal and Torres Strait Islander*, *not Aboriginal or Torres Strait Islander*). Socioeconomic status will be assessed using the 4-item Family Affluence Scale [39,40].

#### Primary Outcomes

##### Alcohol Use

Alcohol use will be assessed using measures previously used in *Climate Schools* trials [17,21,41], originally adapted from the National Drug Strategy Household Survey [42]. Students will be asked how often they had a standard drink in the previous 6 months (from 1=*Never* to 6=*Daily or almost daily*). This question will be accompanied by a standard drink chart from the Alcohol and Drug Foundation [43] as a guide.

##### Tobacco Use

Tobacco use will be measured using a single item adapted from the Standard High School Youth Risk Behavior Survey [44] that asks how often students had a cigarette in the previous 6 months.

##### Psychological Distress

Students will complete the 5-item Kessler Psychological Distress Scale, which has been validated for use with Aboriginal populations [45,46]. Students will be asked to indicate how often in the previous 4 weeks they experienced symptoms of psychological distress, such as feeling nervous, using a 5-point Likert-type scale ranging from *None of the time* to *All of the time*.

#### Secondary Outcomes

##### Cannabis Use

Any cannabis use in the previous 6 months will be assessed using measures adapted from the National Drug Strategy Household Survey [42] for use in previous *Climate Schools* trials [17,21,41]. This outcome will not be assessed in all schools because of differing ethics committee requirements.

##### Binge Drinking

Binge drinking will be assessed using a measure adapted from the School Health and Alcohol Harm Reduction Project [12] for previous *Climate Schools* [17,21,41] trials. Students will be asked how often they consumed ≥5 drinks in the previous 6 months (on a 6-point scale from *Never* to *Daily or almost daily*).

##### Alcohol-Related Harms

A 9-item version of the Rutgers Alcohol Problems Index [47] abbreviated for use in the *Climate and Preventure* study [48] will be used to measure students’ experience of alcohol-related harms. Students will be asked to indicate how often they experienced a range of alcohol-related harms in the previous 6 months as a result of their drinking, using a 5-point Likert-type scale ranging from *Never* to *More than 6 times*. Examples of items include *Got into fights, acted bad, or did mean things* and *Caused shame or embarrassment to someone*.

##### Knowledge of Harms and Risk Minimization Strategies Related to Alcohol, Tobacco, and Cannabis

Alcohol (11 items) and cannabis (8 items) knowledge will be assessed using items adapted from the School Health and Alcohol Harm Reduction Project [12], as used in previous *Climate Schools* studies [13,21,22,25]. Tobacco knowledge will be assessed using an 8-item scale adapted from questions used in the *Health4Life* study [49], the School Health and Alcohol Harm Reduction Project [12], and the Life Skills Training questionnaire [50]. For all knowledge measures, students will be asked to respond *true*, *false*, or *don’t know* to statements such as *You can get addicted to cannabis*.

##### Intentions to Use Alcohol, Tobacco, and Cannabis

Intentions to use AODs will be assessed using a single item, which asks how likely students are to try alcohol, tobacco or cannabis in the next 12 months, and measured on a 5-point scale from *Very unlikely* to *Very likely*. This measure has been used in previous *Climate Schools* studies [17,21].

##### Psychological Well-being

The well-being of the students will be measured using the 7-item Personal Well-being Index-School Children scale, which has been validated for use with Aboriginal, Torres Strait Islander, and non-Indigenous young people [51,52]. Students will be asked to indicate their agreement with statements such as *How happy are you with your health?* using an 11-point scale ranging from 1=*Very sad* to 11=*Very happy*.

##### Empowerment

Empowerment will be assessed using the 14-item Emotional Empowerment Scale from the Growth and Empowerment Measure, which has been developed and validated for use with Aboriginal and Torres Strait Islander Australians [53]. Students will be asked to indicate their level of agreement with statements according to *the way you usually feel about yourself most of the time* using a 5-point scale ranging from a negative (score of 1) to a positive (score of 5) statement. Example items include scales ranging from *I feel like I don’t know anything* to *I am knowledgeable about things that are important to me* and from *I feel slack, like I can’t be bothered do things even when I want to* to *I am strong and full of energy to do what is needed*.

##### Appreciation of Cultural Diversity

To assess the attitudes of the students toward cultural diversity, the adapted 8-item Diversity Attitudes scale from the Civic Attitudes and Skills Questionnaire [54] will be used. Responses will be on a 5-point Likert scale, ranging from *Not at all* to *Very much*. Example items include *I have a strong interest in hanging out with people from different backgrounds* and *Cultural diversity within a group makes a group more interesting and effective*.

##### Truancy

Days absent from school without explanation will be obtained from schools, where possible and permitted by ethics committee requirements.

#### Process Outcomes

##### Appropriateness and Relevance

Students will be asked for feedback on *Strong & Deadly Futures* in the postprogram survey using a 13-item measure adapted from previous *Climate Schools* studies [17]. Students will be asked to rate aspects of the program (overall opinion, lessons, cartoons, activities, relevance, and helpfulness) on a scale of 1-5. Students will also be asked whether they think the skills and information will help them deal more effectively with peer pressure, stress, and drugs and alcohol in the future. Responses will be on a 4-point scale from *Yes, I think they will help a great deal* to *No, I don’t think they will help at all*.

##### Implementation Fidelity

Teachers in both groups will complete web-based logbooks recording lesson procedures and activities as a measure of implementation fidelity. Teachers in Strong *& Deadly Futures* schools will be asked how the stories were viewed (collectively or individually), which activities were completed, whether any issues were encountered, and to record any adaptations they made to the lessons. Local facilitators in *Strong & Deadly Futures* schools will record their observations of student engagement, classroom activities implemented, and any issues the students experienced during class lessons. Teachers in control schools will record summaries of AOD education delivered.

#### Analysis

Because of the hierarchical nature of the data, outcome analyses will use multilevel mixed effects regression models (modeled using Stata [StataCorp LLC]) and take into account clustering of data at the school level. Multilevel modeling accounts for the expected correlations between repeated measurements from the same individual and between individuals in the same school, which would otherwise violate the assumptions of independence in traditional regression models. The models will take into account individual differences at baseline, estimating participant-specific starting points and change over time from these baseline levels. The randomly allocated groups (*Strong & Deadly Futures* vs *health education as usual*) will be identified by dummy-coding and entered as an independent variable. Hypothesized program effects on alcohol and tobacco uptake, psychological well-being, and secondary outcomes will be assessed by examining the allocated group-by-time interaction effects. Primary analyses will examine program effects specifically among Aboriginal and Torres Strait Islander students, with a secondary analysis conducted on the full sample. All analyses will be conducted according to the intention-to-treat principle, using all available measurements from the participants and according to their allocated group. Missing data will be accommodated based on all available information using maximum likelihood estimation.

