#### Study Design and Randomization

This study will use a 2-group, parallel cluster RCT design. Cluster randomization by schools will be implemented, as randomizing individual students within schools would risk contamination of the control group because of student communication and peer influence effects. Recruited schools will be block randomized (ratio 1:1), stratified by geographical remoteness, to the *Strong & Deadly Futures* group (to implement the program in 2022) or the active control condition (*health education as usual* group). Allocation will be concealed and implemented by an independent statistician using the *blockrand* function in R (R Foundation for Statistical Computing) [29]. Remoteness will be classified using the Remoteness Areas structure within the Australian Statistical Geography Standard [30] and defined as metro or inner regional (major cities and inner regional) and outer regional or remote (outer regional, remote, and very remote). Randomization will occur as soon as a school is recruited and before the community consultations. To ensure that consultations are not influenced by randomization, consultation protocols will prescribe set questions for all sessions. If possible, researchers, facilitators, and participants will remain blind to allocation for the consultations; however, this will depend on consultation timing because of the requirement for schools to have sufficient time to plan class schedules. As schools and teachers play an active role in implementing the program, all schools, facilitators, and researchers will be unblinded before the trial. An overview of the study design is shown in Figure 1.

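### Schools are randomized within two remoteness strata, but the described analysis model does not include that factor; if remoteness predicts change in the outcome, some precision is lost

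*Protocol article*

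**What the plan says.** Under Study Design and Randomization: "Recruited schools will be block randomized (ratio 1:1), stratified by geographical remoteness". The factor has two levels: major cities with inner regional areas, and everything more remote. Each school is randomized once it is recruited.

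Under Analysis, the article describes multilevel mixed models that "take into account clustering of data at the school level". On baseline: "The models will take into account individual differences at baseline, estimating participant-specific starting points and change over time from these baseline levels". The arms "will be identified by dummy-coding and entered as an independent variable", and hypothesized program effects "will be assessed by examining the allocated group-by-time interaction effects". Intention to treat and maximum likelihood complete the description. Remoteness does not appear in that section. Other covariates are neither listed nor excluded.

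Under Sample Size Calculations, "a minimum of 264 Aboriginal or Torres Strait Islander students from 22 schools is required", and "This would achieve 80% power to detect a standardized between-group mean difference of 0.3". The recruitment target is 24 schools with an average of 16 such students each, allowing for 30% attrition. That section does not mention remoteness either.

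**The concern.** Stratifying by remoteness removes between-stratum differences from the true sampling variance of the treatment effect. A model without the stratum still counts those differences as error. Its standard error is then larger than the design warrants, and the test falls below its nominal level.

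With 24 schools, between-school variation is what the trial can least afford to leave unexplained. The variable is already held, because it was needed to randomize. Since schools are randomized one at a time within blocks, the last block in a stratum may also be incomplete, so exact balance by stratum is not assured at analysis.

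The tested effect is a difference in change. What matters is therefore whether remoteness predicts change over time, not whether remote and metropolitan schools differ in level.

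**Working it through.** **Inputs from the article:** 24 schools, 16 Aboriginal or Torres Strait Islander students per school, 30% attrition, 4 occasions, effect size 0.3, 80% power, P=.05 (taken as two-sided).

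**Inputs not in the article, hence assumed:** within-student correlation, school ICC, and the share of between-school variance in change that remoteness explains.

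**1. The plan's own figure.** For a group-by-time effect, schools per arm = 2(1−ρ)(z₀.₉₇₅+z₀.₈₀)² / (N₁·N₂·Var(T)·Δ²). Take 4 occasions at T = 0 to 3 (Var(T) = 1.25), 12 students per school, Δ = 0.3/3 = 0.1, and (z₀.₉₇₅+z₀.₈₀)² = 7.849.
- ρ = 0.58: 2 × 0.42 × 7.849 / 0.6 = 10.99.
- ρ = 0.60: 2 × 0.40 × 7.849 / 0.6 = 10.47.

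Both round up to 11 per arm, so 22 schools and 264 students. As ρ is not stated, the printed figure is consistent with this formula but not independently confirmed. On attrition, 384 × 0.70 = 268.8, which exceeds 264. No stratum term enters, so this point does not alter the stated sample size.

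**2. A main effect alone.** With complete data, 192 students per arm, ρ = 0.6 and Σ(t−t̄)² = 5, the SE of the 24-month group-by-time effect is 3 × √(2 × 0.4 / (192 × 5)) = 0.0866. The school and student intercept variances do not appear in it. A remoteness main effect can reduce only the school intercept variance, so it cannot help here. A generalized least squares check with fixed variance components (ICC 0.05) gave 0.0866 with and without the main effect, and 0.0987 with and without it under 30% dropout. Adding stratum-by-time also left these values unchanged. Its benefit comes only through a smaller estimated between-school variance in change.

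**3. Stratum by time, if remoteness predicts change.** Students per school at the end: 16 × 0.70 = 11.2. Let ICC be the ICC of change and R the share of between-school variance in change that remoteness explains.
- Unadjusted factor: 1 + 10.2 × ICC.
- Factor with the stratum removed: (1−ICC) + 11.2 × ICC × (1−R).
- Size of the unadjusted test: 2(1−Φ(1.96/√ratio)).

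| ICC of change | R | Unadjusted | Adjusted | Ratio | Variance cut | Size, unadjusted |
|---|---|---|---|---|---|---|
| 0.05 | 20% | 1.51 | 1.398 | 0.926 | 7% | 4.2% |
| 0.05 | 30% | 1.51 | 1.342 | 0.889 | 11% | 3.8% |
| 0.05 | 50% | 1.51 | 1.230 | 0.815 | 19% | 3.0% |
| 0.02 | 20% | 1.204 | 1.159 | 0.963 | 4% | – |
| 0.02 | 30% | 1.204 | 1.137 | 0.944 | 6% | – |
| 0.02 | 50% | 1.204 | 1.092 | 0.907 | 9% | – |

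**4. Simulation.** School-level change scores were simulated for 24 schools, balanced 1:1 within two strata of 12, with 100,000 replicates per setting. Here R² is the share of the total variance of school-mean change due to remoteness. The ICC 0.05 rows above correspond to R² of about 0.07, 0.11 and 0.19 (for example, 0.20 × 0.56/1.51 = 0.074).

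| R² | Type I error without / with stratum | Power without / with stratum |
|---|---|---|
| 0 | 0.050 / 0.050 | 0.80 / 0.80 |
| 0.05 | 0.045 / 0.051 | 0.81 / 0.82 |
| 0.10 | 0.039 / 0.050 | 0.81 / 0.84 |
| 0.25 | 0.024 / 0.050 | 0.82 / 0.90 |

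A 16:8 split of schools between strata gave nearly the same results.

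**The case against.** The strongest reply is that this is one paragraph in a journal article. Covariate lists are commonly left to the SAP or full protocol, neither of which is shown, and nothing in the article rules remoteness out. This stands as a limit on the point. A reader might infer that the model contains only arm and time, but the text does not say so: it also describes school clustering, participant-specific starting points and change from baseline, and its silence on covariates is not an exclusion. The point survives as an improvement because the paragraph does set out its main fixed effects, and the one that follows from the randomization is not among them.

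A reader might also infer that precision is certainly lost. The documents do not support that either. They give no ICC and no sign that remoteness predicts change. An ordinary school ICC for outcome level cannot be put into step 3, because level differences cancel from change.

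Finally, a conservative test follows only if the model estimates between-school variance in change, for instance through a school-level random slope, and the article does not say whether it does. With a school random intercept only, at ICC 0.05 and R = 30%, the true variance factor of 1.342 would face a modelled factor of about 1.0. The size would be 2(1−Φ(1.96/√1.342)), about 9%. That inflation would come from unmodelled school-by-time variation, not from the missing stratum, and adding the stratum would not cure it. It does mean that the direction of error cannot be asserted with high confidence.

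**Conclusion.** The point holds in a limited, conditional form. The randomization uses a factor that the described model does not include. Where remoteness predicts change and between-school variance in change is estimated, leaving it out makes intervals somewhat too wide and the test somewhat conservative. Bias and false-positive inflation do not arise by this route. In the simulation the power forgone is nil at R² = 0, about 1 point at 0.05, about 3 at 0.10 and about 8 at 0.25; power without the stratum stays at 0.80 to 0.82 over that range.

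These sizes rest on assumed values for the ICC of change and the explained shares, on equal school sizes, and on an approximately linear, normal model. The stated sample size is unaffected. This is an inexpensive gain worth taking, not a demonstrated error in the analysis.

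**What to change.** Unless the SAP already does so, state that the two-level remoteness stratum and its interaction with time enter as fixed effects in the primary and secondary models. Both terms are needed, because the effect under test is a difference in change. The same sentence should say whether the model estimates between-school variance in change, since the benefit depends on it.

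The cost is one line of analysis text and syntax and one school-level degree of freedom (24 − 2 = 22 becomes 24 − 3 = 21). No new data are needed. The change should be fixed before outcome data are examined by arm.
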